### Ethics issues

The study protocol and consent forms have been approved by the Ethics Committee of Renji Hospital (NO: Renji Lunshen [2016] 001(2)) and the local institutional review boards of each participating site (Additional file 2). The trial is registered on ClinicalTrials.gov with ID number NCT02645578 and will be performed in accordance with the Declaration of Helsinki and the guidelines of Good Clinical Practice.

Theoretically, all patients should sign an informed consent form in person before enrolment. Due to the nature of TBI, the patients will not be physically or mentally capable of giving consent. A legal representative will be approached to give assent for participation in the trial after explanation by an investigator. The legal representative will usually be a family member or the closest relative who can make the decision on behalf of the patient. If no legal representative is available in due time, an independent staff member from the local institutional review boards who is not involved in the trial will be asked for study approval.

### Randomisation and allocation concealment

Participants at each site will be randomly assigned in a ratio of 1:1, stratified by study centre, to the stimulation group or the non-stimulation group, using a block-randomisation scheme. The whole randomisation procedure will be carried out by independent statisticians who are not involved in the determination of the final result. The trial secretary will place the computer-generated randomisation sequence and treatment assignment together into opaque envelopes and seal and mail these envelopes to each participating centre. After each patient is stabilised, assessed and identified as possibly meeting the criteria, a study physician at each local centre will do the group assignment by opening sequentially numbered envelopes.

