### Inclusion and exclusion criteria for the trial

Patients who meet the following criteria will be deemed eligible for the trial: (1) admitted to the hospital due to closed TBI 7 to 14 days previously; (2) GCS score of 4–8 or GMS below 5 on admission; and (3) aged 18–65 years old.

Those who meet the following criteria will be excluded from the trial: (1) vital signs not stable; (2) admitted to hospital due to penetrating cranial injury; (3) a confirmed history of epilepsy before enrolment or during the time of hospitalisation; (4) severe cardiac arrhythmia or pacemaker implanted; (5) pregnancy; and (6) no consent form.

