### Treatment protocol

After being admitted to the hospital, all patients will be assessed and receive standard treatment (including surgery, if necessary) in the neurology ICU in accordance with the current guidelines [25]. Those who meet the criteria and whose representative has signed an informed consent form will be enrolled in the trial and be randomly assigned to the stimulation or non-stimulation group according to the procedure mentioned above.

The patients in the stimulation group will receive RMNS in addition to standard treatment. The electrical treatment will be delivered via a pair of lubricated 1-inch square rubber surface electrodes pasted 1 inch apart on the volar aspect of the right distal forearm over the median nerve. An electrical neuromuscular stimulator (Verity Medical Ltd., Braishfield, UK) will supply trains of asymmetric biphasic pluses at an amplitude of 15–20 mA (as tolerated) with a pulse width of 300 μs at 40 Hz ON for 20 s and OFF for 40 s, which has been proven to be well tolerated without causing pain or skin irritation. The electrical stimulation treatment will last for 8 h per day for 2 weeks. Patients assigned to the control group will continue to receive the previous standard treatment without electrical stimulation. During treatment, all patients will receive intensive care to prevent hypotension, hypoxia, intracranial hypertension and disturbance of homeostasis.

In addition to vital signs and general data, some additional data from the case report forms (CRFs) will be assessed at the beginning of the trial and during treatment. Once enrolled in the trial, the GCS, Glasgow Coma Scale Motor Part (GMS), Full Outline of Unresponsiveness (FOUR) scale, Coma Recovery Scale-Revised (CRS-R) and Disability Rating Scale (DRS) scores of each patient will be collected.

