#### Statistical analysis

Analysis will be performed in accordance with the intention-to-treat principle. All randomised patients will be included in their original assigned group regardless of the actual treatment approach they receive. Categorical variables will be described as numbers and percentages and analysed by the chi-squared test. Normally distributed continuous variables will be presented as mean and standard deviation (SD) and compared using Student’s *t* test; non-normally distributed variables will be expressed as median and interquartile ranges and analysed using the Mann–Whitney U test. A two-sided significance level of 0.05 will be used.

Baseline data such as age and GCS score at admission will be tested for any imbalance. If imbalances are detected, those factors will be corrected using a multiple logistic regression model.

The primary endpoint, namely the percentage of patients regaining consciousness 6 months after injury, will be presented as total percentage per group and analysed as categorical variables. The secondary outcome variables describing clinical status throughout the treatment and follow-up will be analysed as continuous variables.

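### The envelope may be opened for a patient who only possibly qualifies, which conflicts with the treatment section and leaves room to settle eligibility after the arm is known

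*Protocol article*

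**What the plan says.** Two sections of the protocol article give the condition for allocation.

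- *Randomisation and allocation concealment*: for a patient who has been stabilised and assessed, the rule continues: "identified as possibly meeting the criteria, a study physician at each local centre will do the group assignment by opening sequentially numbered envelopes". Consent is not mentioned here.
- *Treatment protocol*: "Those who meet the criteria and whose representative has signed an informed consent form will be enrolled in the trial and be randomly assigned". For the method, this section points back: "according to the procedure mentioned above".

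Two other sections bear on the point. Under *Inclusion and exclusion criteria for the trial*, the exclusions begin "1) vital signs not stable" and end "5) pregnancy; and (6) no consent form", so consent is itself one of the criteria. Under *Statistical analysis*, the analysis set is fixed: "All randomised patients will be included in their original assigned group regardless of the actual treatment approach they receive".

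**The concern.** Opening the envelope is the one step that cannot be undone. The section that describes it sets a lower threshold (possibly eligible) than the section that says who is randomised (eligible, with consent signed). A site that follows the envelope section literally may still have criteria to confirm when it learns the arm.

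This matters more than usual here because controls receive standard care without stimulation, so treating staff know the arm from that moment. A later eligibility decision could then be influenced by the arm. Even without any such influence, patients who never qualified would enter the analysis and pull the two arms together.

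**Working it through.** **Step 1. The two triggers side by side.**

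| | Randomisation section | Treatment section |
|---|---|---|
| Eligibility | possibly meets the criteria | meets the criteria |
| Stability | required before opening | covered by the criteria |
| Consent | not mentioned | signed before randomisation |
| Procedure | site physician opens the next envelope | refers back to the envelope procedure |

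The eligibility row is a direct conflict. The consent row is silence on one side and an explicit order on the other.

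**Step 2. Which rule governs.** The randomisation section is the only one that describes the envelope, and the treatment section sends the reader there. *Data collection and follow-up* mentions enrolment and randomisation together and does not fix their order relative to final eligibility checks. Nowhere does the article say that eligibility must be confirmed before opening.

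**Step 3. What happens to a patient found ineligible after opening.** There are two possibilities. If opening the envelope counts as randomisation, the analysis rule keeps the patient, and the effect is diluted. If it does not count, the patient can be dropped after the arm is known. The article calls the opening of the envelope group assignment, which favours the first reading, but it does not state that this is the moment of randomisation.

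**Step 4. Size of dilution, as an illustration.** Inputs from *Sample size justification*: 59.8% with stimulation and 46.2% without. The planned difference reproduces: 59.8 − 46.2 = 13.6 points. Assumed, not in the documents: a share f of each arm is ineligible, and these patients recover at 46.2% in either arm.

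Stimulation-arm rate = (1 − f) × 59.8 + f × 46.2

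- f = 5% (19 of 380): 0.95 × 59.8 + 0.05 × 46.2 = 59.1%. Difference 0.95 × 13.6 = 12.9 points.
- f = 10% (38 of 380): 0.90 × 59.8 + 0.10 × 46.2 = 58.4%. Difference 0.90 × 13.6 = 12.2 points.

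**Step 5. Power, with a caution.** For 190 per arm and a two-sided 0.05 test, power = Φ((d − 1.96 × SE0) / SE1). Here d is the difference, SE0 = √(2 p̄ (1 − p̄) / 190) with p̄ the mean of the two rates, and SE1 = √((p1(1 − p1) + p2(1 − p2)) / 190).

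- No dilution: (0.136 − 1.96 × 0.05121) / 0.05073 = 0.70, power 75.9%.
- f = 5%: (0.1292 − 1.96 × 0.05123) / 0.05080 = 0.57, power 71.5%.
- f = 10%: (0.1224 − 1.96 × 0.05124) / 0.05086 = 0.43, power 66.7%.

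The undiluted 75.9% differs from the article's stated 84%. That gap is a separate sample-size question and is not caused by the envelope wording. Only the fall from the starting value belongs here.

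**The case against.** The two sections can be read together: the treatment section says who is randomised, the randomisation section says how, and one adverb may be loose writing. Patients must already be stabilised and assessed before the envelope is opened. Most criteria, such as age, type of injury, the coma score on admission and a pacemaker, would ordinarily be known after 7 to 14 days in hospital. The analysis rule also forbids dropping randomised patients.

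Much of this stands. Stability of vital signs is not a good example of a criterion settled late, and the number of patients affected may be small. It does not remove the conflict, because the looser wording sits in the section that governs the act, and some exclusions (whether an arrhythmia is severe, for instance) need judgement.

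A reader might infer three stronger conclusions that the documents do not support.

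- *That allocation concealment is broken.* The sequence is computer-generated, and the envelopes are opaque, sealed and sequentially numbered. Nothing in this wording reveals the next assignment before an envelope is opened. The issue is what may be decided afterwards.
- *That consent is placed after allocation.* The randomisation section is silent on consent. The treatment section, the ethics section and the last exclusion criterion all put it before entry.
- *That bias from selective removal has no limit.* The endpoint is binary, so any assumed removal rate sets a limit. If 10% of the stimulation arm were removed, all of them failures, 59.8% would become 59.8 / 0.90 = 66.4%. If 10% of controls were also removed, all of them successes, 46.2% would become (46.2 − 10) / 0.90 = 40.2%. The difference would be 26.2 points instead of 13.6, a bias of 12.6 points. That is the extreme case, and nothing suggests that it occurred.

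**Conclusion.** The point holds as an inconsistency between two sections with a consequence for the analysis set. As written, the envelope section permits remaining eligibility judgements after the arm is known; it does not show that this has happened. The result would be either dilution, if ineligible patients are kept, or removal after allocation, which would go against the intention-to-treat rule and could bias the comparison.

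The documents do not allow the size to be derived. The reduction from 13.6 to between 12.9 and 12.2 points rests entirely on the assumed 5% to 10% of ineligible patients and on their gaining nothing from stimulation. The correction is worth making because it is cheap and the article reports that recruitment is still under way.

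**What to change.** Make two changes in *Randomisation and allocation concealment*.

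1. Replace the clause on possible eligibility by: *confirmed as meeting all inclusion and exclusion criteria, with consent documented*. This brings the section into line with *Treatment protocol*.
2. Add: *A patient counts as randomised once the envelope is opened, and is analysed in the assigned group under the intention-to-treat rule.*

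The cost is two sentences and a notice to the sites, with no extra staff and no change to the allocation scheme. Site-level aids such as a checklist or a reconciliation of envelope numbers may already be in the full protocol, and their absence from the article is not a fault.

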### Treatment protocol

After being admitted to the hospital, all patients will be assessed and receive standard treatment (including surgery, if necessary) in the neurology ICU in accordance with the current guidelines [25]. Those who meet the criteria and whose representative has signed an informed consent form will be enrolled in the trial and be randomly assigned to the stimulation or non-stimulation group according to the procedure mentioned above.

The patients in the stimulation group will receive RMNS in addition to standard treatment. The electrical treatment will be delivered via a pair of lubricated 1-inch square rubber surface electrodes pasted 1 inch apart on the volar aspect of the right distal forearm over the median nerve. An electrical neuromuscular stimulator (Verity Medical Ltd., Braishfield, UK) will supply trains of asymmetric biphasic pluses at an amplitude of 15–20 mA (as tolerated) with a pulse width of 300 μs at 40 Hz ON for 20 s and OFF for 40 s, which has been proven to be well tolerated without causing pain or skin irritation. The electrical stimulation treatment will last for 8 h per day for 2 weeks. Patients assigned to the control group will continue to receive the previous standard treatment without electrical stimulation. During treatment, all patients will receive intensive care to prevent hypotension, hypoxia, intracranial hypertension and disturbance of homeostasis.

In addition to vital signs and general data, some additional data from the case report forms (CRFs) will be assessed at the beginning of the trial and during treatment. Once enrolled in the trial, the GCS, Glasgow Coma Scale Motor Part (GMS), Full Outline of Unresponsiveness (FOUR) scale, Coma Recovery Scale-Revised (CRS-R) and Disability Rating Scale (DRS) scores of each patient will be collected.

### Study endpoint

The primary endpoint is the percentage of patients regaining consciousness 6 months after injury. The degree of consciousness can be divided into three categories: VS, MCS and consciousness (CS). The diagnosis of consciousness includes complete wakefulness and awareness of self and environment, precise comprehension and interaction, correct orientation of figures, time and location, the ability to obey commands and intact light and deep reflexes [24]. In the ACES trial, we will focus on the percentage of patients regaining consciousness 6 months after injury. This parameter indicates the long-term effect of RMNS.

The secondary endpoints are GOSE, CRS-R and DRS scores 28 days, 3 months and 6 months after injury and GCS, GMS and FOUR scores day 1 and day 7 after enrolment and 28 days, 3 months and 6 months after injury. Duration of unconsciousness and mechanical ventilation, and length of ICU and hospital stays will also be recorded as secondary endpoints.

The safety of RMNS will be assessed by the incidence of adverse events within 6 months post injury, including but not limited to (1) seizures, (2) increased intracranial pressure and (3) intracranial bleeding.

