Non-randomised controlled trial studies and reviews, although not as convincing, also indicate that RMNS may play a role in the emergence from coma following severe brain injury. For example, Liu and colleagues used RMNS on six comatose patients for 3 months. Four patients regained consciousness within 35 days, and brain perfusion increased in all six cases assessed by single-photon emission computed tomography (SPECT) scans after stimulation [20]. A review by Cooper and colleagues concluded that RMNS is a promising therapy for the neuroresuscitation of comatose patients, and time in the ICU may be shortened and the quality of the final outcome enhanced when the stimulation is applied early in the coma [18].

The trials selected had limitations due to the small number of cases analysed in most studies, inappropriate methods of randomisation in some cases, the diversity in coma length and coma severity, the heterogeneity of outcome measures, the different timing of intervention and follow-up and the lack of multicentre studies. We designed the ACES trial with an adequate sample size and a standardised protocol to obtain convincing evidence about the efficacy and safety of RMNS in both accelerating emergence from coma and promoting long-term outcomes.

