### Statistics and data analysis

#### Sample size justification

The required sample size is calculated based on the results of our previous randomised controlled trial [24]. In that study, the proportions of patients regaining consciousness in the RMNS and non-stimulation groups were found to be 59.8% and 46.2%, respectively. Thus, to detect a difference of not less than 13.6% (the difference between 59.8% and 46.2%) between the experimental group and the control group, 334 patients will be needed with an α value of 0.05 and a power of 0.8. To allow for some patients lost to follow-up, a sample size of 380 in total (190 for each group) has therefore been chosen, which gives 84% power to detect the same difference at the same significance level.

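### The only tests the plan states for coma, ventilation and stay durations make no provision for death or non-waking, yet about 47% of patients would not be fully conscious by 6 months

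*Protocol article*

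**What the plan says.** The protocol article, under Study endpoint, lists four durations among the secondary endpoints: "Duration of unconsciousness and mechanical ventilation, and length of ICU and hospital stays will also be recorded as secondary endpoints".

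Under Statistical analysis, normally distributed continuous variables are compared by Student's t test, and "non-normally distributed variables will be expressed as median and interquartile ranges and analysed using the Mann–Whitney U test". The same section includes every randomised patient in the assigned group. It adds that secondary outcomes describing clinical status are treated as continuous. It mentions no censoring, no competing event, and no value or rank for a patient who dies or does not wake.

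Under Sample size justification, the proportions regaining consciousness in the earlier trial "were found to be 59.8% and 46.2%, respectively", for stimulation and control. The article carries these over to its own endpoint: "The primary endpoint is the percentage of patients regaining consciousness 6 months after injury". Under Data collection and follow-up, the date of regaining consciousness and all deaths are recorded. The Background gives the trial's purpose as evidence on the "efficacy and safety of RMNS in both accelerating emergence from coma and promoting long-term outcomes".

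**The concern.** A t test or Mann–Whitney test needs a value for every patient. A patient who is still not conscious at 6 months, or who dies before waking, has no completed duration of unconsciousness. Two simple ways of applying the stated tests are open, and both are unsound:

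- **Analyse only those who woke.** The comparison is then restricted by the outcome that treatment is meant to change, and the randomised groups are no longer compared.
- **Enter time to death or last contact as the duration.** An early death then counts as a short coma. Ventilation, ICU stay and hospital stay have the same fault, because a patient who dies early has a short stay.

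Faster emergence from coma is one of the trial's two stated aims, and duration of unconsciousness is the endpoint that measures time to waking directly. An analysis that loses or reverses the effect could mislead on that aim even if the primary analysis is sound.

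**Working it through.** **1. The planning rates.** The inputs are 59.8% and 46.2%, with 1:1 allocation of 380 patients (Sample size justification). The pooled two-proportion formula is n per arm = [z_α√(2p̄q̄) + z_β√(p₁q₁ + p₂q₂)]² / d², with p̄ = 0.53, d = 0.136, 2p̄q̄ = 0.4982 and p₁q₁ + p₂q₂ = 0.4890.

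- One-sided α of 0.05: (1.645 × 0.7058 + 0.842 × 0.6992)² / 0.0185 gives 166 per arm, 332 in total. The article states that "334 patients will be needed with an α value of 0.05 and a power of 0.8". Power at 190 per arm is 84.6%, against the stated 84%.
- Two-sided α of 0.05: 211 per arm, 422 in total, and 75.9% power at 380.

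The rates are therefore the ones behind the stated figures. That these figures match only a one-sided test is a separate matter.

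**2. Patients with no observed end of unconsciousness.**

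- Stimulation: 1 − 0.598 = 40.2%; 190 × 0.402 = 76.4.
- Control: 1 − 0.462 = 53.8%; 190 × 0.538 = 102.2.
- Total: 178.6 of 380 = 47.0%.
- Expected awakenings: 190 × (0.598 + 0.462) = 201.4.

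**3. Wakers-only comparison: effect of timing.** The documents give no waking times, so everything here is assumed. Suppose nobody is delayed and stimulation adds 13.6 points of awakenings. The added wakers are 0.136 / 0.598 = 22.7% of stimulation-arm wakers. The shift in mean duration among wakers is 0.227 × (mean of added wakers − mean of other wakers). With an assumed mean of 45 days for the other wakers:

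| Assumed timing of added awakenings | Mean of added wakers (days) | Shift in mean (days) | Simulated share of trials in which Mann–Whitney calls stimulation longer |
|---|---|---|---|
| Days 14–60 | 37 | −1.8 | about 0.5% |
| Same as other wakers | 45 | 0 | about 2% |
| Days 21–90 | 55.5 | +2.4 | about 11% |
| Days 14–180 | 97 | +11.8 | about 37% |
| Days 60–180 | 120 | +17.1 | 64% to 75%, by shape of waking times |

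The last column is from simulation with 190 per arm and a median of about 39 days in control wakers.

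**4. Hidden benefit, and cutting at death.** A second simulation used 2,000 runs and 190 per arm. Waking fell between days 14 and 180, non-wakers alive at the end were set to day 180, and the death rates were assumed. The figures are rejection rates of the Mann–Whitney test at 0.05:

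| Scenario | Wakers only | Cut at death | Deaths and non-wakers ranked worst |
|---|---|---|---|
| Waking 59.8% vs 46.2%, same timing among wakers, deaths 15% in each arm | 4.6% | 64.2% | 66.6% |
| Waking 46.2% in both arms, deaths 25% vs 10% | 5.3% | 76.5% | 5.3% |
| Waking 46.2% in both arms, deaths 15% in each arm | 6.0% | 4.8% | 4.8% |

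In the first row, wakers-only loses a real benefit. In the second, there is no difference in waking, but the arm with more deaths looks about 19 days better when durations are cut at death. The third row shows that this fault needs unequal mortality.

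**5. Ventilation and stay.** If survivors average S days and deaths D days, the arm mean is (1 − m)S + mD, where m is mortality. The arm with lower mortality looks worse by (difference in m) × (S − D). With assumed S = 30, D = 10 and mortality of 20% vs 15%, the means are 26 and 27 days: 0.05 × 20 = 1 day. With a 15-point mortality difference it would be 3 days. Only the direction is informative.

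**The case against.** The strongest reply is that the article does not say the durations will be treated as complete values. The sentence on continuous secondary outcomes refers to clinical status and may mean the scale scores only. The article points to a separate predetermined analysis plan, which could rank deaths and non-wakers worst within a Mann–Whitney test and so stay within the published wording. This stands as far as it goes: the fault is in what the published text offers, and the unseen plan may already contain a remedy. It does not remove the point. The general rule for continuous variables is the only one in the article that could cover the durations, and neither test handles censoring or death without a further rule.

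A reader might infer that the stated tests will give the wrong sign. The documents do not support that. Reversal needs a wakers-only analysis, which the intention-to-treat commitment argues against, and late extra awakenings. With all randomised patients kept, non-wakers set at 6 months and no early deaths, the days 60–180 scenario gave a stimulation arm 8.5 days shorter on average. Mann–Whitney then called it shorter in 30% of trials and never longer.

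Three further limits stand:

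- The death bias needs unequal mortality, and no mortality figure is given.
- The 47% counts everyone short of full consciousness, including the minimally conscious. It applies only if unconsciousness ends at the protocol's definition of consciousness, and it says nothing about ventilation or stay.
- The Discussion names the GCS, its motor part and the FOUR score as the recovery-pace measures, so duration of unconsciousness is not the only endpoint bearing on speed.

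**Conclusion.** The concern holds in limited form. The published method for the four duration endpoints makes no provision for death or non-waking. On the article's own rates, about 179 of 380 patients (47%; 40.2% and 53.8% by arm) would have no observed end of unconsciousness. This assumes, as the article does, that the earlier trial's rates apply at 6 months.

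A wakers-only analysis would contradict the intention-to-treat rule. It would miss a benefit when timing among wakers is equal (about 5% rejection), and could reverse the sign when extra awakenings are late. Cutting at death is biased when mortality differs between arms, by an amount the documents do not allow one to calculate. All the simulated figures rest on assumed waking times and death rates.

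Only secondary endpoints are concerned; the binary primary endpoint is unaffected. The change should be made before database lock, but it does not put the trial's main conclusion at risk.

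**What to change.** - **Unconsciousness.** Analyse time from randomisation to first regaining consciousness, as defined under Study endpoint, in all randomised patients. Censor at 6 months or last contact and treat death as a competing event: cumulative incidence with Gray's test or a Fine–Gray model, stratified by centre. About 201 waking events would be expected on the planning rates.
- **Minimum alternative.** Use a Mann–Whitney test in all randomised patients, with deaths and non-wakers given the worst ranks.
- **Ventilation, ICU and hospital stay.** Replace each by days alive and free of it from randomisation to a fixed day, with death counted as zero.

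Starting at randomisation leaves out days that treatment cannot affect. This is for clarity: randomisation balances those days, so counting them would not bias the comparison.

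The cost is mainly analysis wording, since waking dates and deaths are already recorded. There are two drawbacks. The results will be less comparable with earlier reports of mean duration. After discharge, patients are assessed only at 1, 3 and 6 months, so some waking dates may be known only to the interval between visits, and the plan should say how these are handled.
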